#### 1. SYNOPSIS

**Background:**

Sodium imbalance is common and an adverse prognostic factor in hospitalized patients. However, identifying the causes of sodium imbalance is challenging in clinical practice. Levels of antidiuretic hormone (ADH) are elevated in patients with stroke correlating with disease severity and stress level; however, its measurement is cumbersome. ADH is derived from a larger precursor peptide along with Copeptin, which is a more stable peptide directly mirroring the production of ADH. Copeptin can be assayed readily in plasma. Early prognostic factors to predict in-hospital mortality and medium/long-term outcome in critically ill neurological patients, are helpful to guide and tailor early decisions on treatment, discharge from the intensive care unit and application of interventions to prevent deterioration of neurological functions.

**Aim:** To evaluate Copeptin as a diagnostic tool in disturbances of water homeostasis and prognostic tool to predict outcome in a well-defined cohort of stroke patients and patients undergoing intracranial surgery.

**Design:** Prospective, observational study.

**Location Setting:** Emergency and neurogical and neurosurgical clinic of the University Hospital of Basel.

**Patients:** Neurological patients with ischemic and hemorrhagic stroke and patients undergoing intracranial surgery.

**Intervention:** After informed consent, all routinely determined baseline data will be assessed including medical history, clinical items (i.e. neurological status, volume status, pulse rate, blood pressure, weight) and laboratory items (i.e. urine / serum osmolality, electrolytes, among others). All patients will have a follow-up with clinical and laboratory assessment until the day of discharge. After 3 months, they will be followed-up by a structured telephone interview to assess outcome (mortality, morbidity, as assessed by the ranking scale and Barthel index). Copeptin will be assessed in a batch analysis upon completion of the plasma asseveration.

**Variables and measurements:** Baseline data on medical history and clinical items, co-morbidities and treatment procedures will be collected. This exploratory study will be conducted over a 12 month period from November 2006 to November 2007.

**Study hypothesis:** 1. Copeptin will improve the diagnostic accuracy to diagnose sodium imbalances as compared to routinely used markers 2. Copeptin will be a reliable prognostic tool, dependent or independent of sodium imbalance, to predict short-term (i.e. in-hospital) and medium-term (i.e. 3 months) clinical outcome in stroke patients. Further other biomarkers will be measured to assess prognostic values.

**Analysis:** Our sample size consideration is based on the second prognostic question to predict the outcome of neurological and neurosurgical patients. To determine an optimal clinical model we will undertake a multivariable regression analysis to assess which variables are independently associated with outcome. Multiple regression models with a minimum of 10 to 15 observations per predictor variable reveal good estimates. We will evaluate 18 predictors in our multivariate analysis. Therefore, we aim to include a minimum sample size of 180 patients (for 10 observations per predictor) to 270 (for 15 observations per predictor) and a maximum sample size of 360 patients (for 20 observations per predictor).

**Significance:** Despite the frequent occurrence and the poor outcomes of serious disorders of sodium balance, few controlled data are available to guide the clinician. A better diagnostic approach to determine the etiology of hyponatremia should improve patient management. Copeptin as a prognostic marker in neurological and neurosurgical patients could become an innovative tool to guide early treatment decisions, discharge from the stroke unit and application of interventions.

**2. RESEARCH PLAN**

**2.1 Introduction**

Disorders of serum sodium are the most common electrolyte disorder in hospital practice [1] and represent a significant healthcare burden [2]. Mild hyponatremia (i.e. plasma sodium 130-135mmol/l) is found in as many as 15-30% of hospitalized patients [3-6]. More severe hyponatremia (plasma sodium <130mmol/l) is seen in 1-4 % of inpatients [7]. Hyponatremia in hospitalized patients has a significant mortality ranging from 5% to 50%, depending on severity and acuity of onset as well as comorbidities. Hypernatremia is far less common but mortality ranges from 60 to 75% [8].

The central nervous system (CNS) plays an integral role in the neuroendocrine regulation of sodium and water homeostasis. Hyponatremia is the most common electrolyte disorder encountered in the neurologic intensive care unit [3,9,10]. It is seen in patients with subarachnoidal hemorrhage (SAH) [11], brain tumors [12-14] and ischemic stroke [15-17], complicating their clinical courses [9]. A timely and accurate diagnosis followed by a correct treatment is crucial [18,19]. Differential diagnoses include the syndrome of inappropriate antidiuretic hormone secretion (SIADH), cerebral salt wasting (CSW), hypo- or hypervolemic hyponatremia, and mixed cases [20]. Besides measurement of plasma osmolality and sodium concentration in urine, determination of the extracellular fluid volume remains the most important discriminatory element. However, its prediction based on clinical signs and routine laboratory evaluation has a limited sensitivity and specificity of <50% [21,22]. Accordingly, only 10% of physicians reach the correct diagnosis of the underlying cause of hyponatremia with the routinely used clinical diagnostic algorithms [23]. Thus, there is demand for more reliable parameters to improve the diagnosis of sodium imbalance in patients with CNS disease.

Plasma sodium concentrations are kept within a narrow range to maintain a constant plasma osmolality. This is predominantly regulated by arginin vasopressin (ADH). ADH is produced in the hypothalamus and stored in and released from the neurohypophysis. Plasma ADH levels begin to fall immediately upon swallowing water, before plasma dilution occurs, allowing prompt excretion of diluted urine [24]. Unfortunately, the measurement of circulating ADH levels is challenging, since the mature hormone is very unstable, largely attached to platelets and rapidly cleared from plasma with a half-life of 5 to 15 minutes. ADH is derived from a larger precursor peptide (pre-provasopressin) along with two other peptides, neurophysin II and copeptin. Released in an equimolar ratio, the amount of copeptin mirrors the production of ADH. Plasma copeptin concentration have recently been shown to be an easy to determine, steady parameter [25,26].

ADH plays not only a critical role in osmo-regulation, but also in the regulation of the hypothalamo-pituitary-adrenal (HPA) axis and, thus, reflecting the individual stress response. “Stressors” such as stroke or hemorrhage are strong stimulators of the release of ADH [27]. Accordingly, elevated ADH levels have been reported in experimental ischemia [28,29]. In a small clinical study, patients with stroke had increased ADH levels as compared to controls, correlating with stroke severity [30]. Early prognostic factors to predict in-hospital mortality and medium/long-term outcome in stroke patients are important to guide and tailor early decision on treatment, discharge from the stroke unit and interventions to prevent deterioration of mobility status. Existing prognostic models for stroke often include impractical predictor variables, lack sufficient predictive accuracy and are, thus, not routinely used. In this context, copeptin may be a new prognostic marker and a helpful tool in the early risk stratification of stroke patients.

**2.2 DETAILED RESEARCH PLAN**

**A. Objectives**

The objectives of this trial are to evaluate

1. The diagnostic value of copeptin levels in the diagnosis of water imbalance in patients with stroke and patients undergoing intracranial surgery.
2. The prognostic accuracy of copeptin levels and other biomarkers to predict the clinical outcome in patients with stroke and patients undergoing intracranial surgery.

Specific objectives of the study are:

- - 1. **Diagnostic Study:**

**Hyponatremia** will be defined as serum sodium concentration below 135 mmol/L [31].

Specifically, we aim to investigate whether Copeptin levels can facilitate the differential diagnosis of hyponatraemia. Thereby, we will use a standardized clinical algorithm based on medical history, drug history, clinical assessment of the extracellular fluid volume, and laboratory parameters such as plasma and urine sodium concentration, plasma and urine osmolality, creatinine, uric acid, urea, total protein, albumin, TSH, fT4, T3, blood glucose, urea nitrogen, plasma potassium to evaluate the aetiology of hyponatraemia (**figure 1**). In our cohort, wee expect a prevalence of around 20 % (i.e. around 75 patients of the 350 patients derived from the power calculation, see below) to have hyponatraemia. The etiologies are listed in Figure 1 including the estimated relative contributions and the most frequent diagnosis within the subgroup is underlined.

**Figure 1** Diagnostic algorithm of hypotonic hyponatraemia:

We **hypothesize** that overall, included patients will have moderately but significantly higher copeptin levels (around 5pmol/L) as compared to healthy controls (4pmol/L). In patients with hyponatraemia, copeptin levels will be lower as compared to patients without hyponatraemia, however, with a wide range (1.7pmol/L (detection limit) to 15pmol/L). Analysing the subgroup of patients with hyponatraemia, we assume that in patients with SIADH, copeptin levels will be markedly increased (i.e. 12pmol/L), moderately increased (8pmol/L) in hypovolemic hyponatraemia and suppressed in hypervolemic hyponatraemia (<2pmol/L). Importantly, we anticipate to identify SIADH as a co-factor also in some patients with “typical” hypervolaemic and hypovolemic hyponatremia, where ADH disturbances have been neglected previously due to the incapability to assess circulating ADH levels.

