**Hypernatremia**

Hypernatremia will be defined as a rise in the serum sodium concentration to a value exceeding 145 mmol/L [3]. Again, we will use a standardized clinical algorithm based on clinical and laboratory parameters to evaluate the aetiology of hypernatraemia.

Of all 350 patients included (see sample size considerations) we expect 10 % (i.e. around 45 patients) to have hypernatraemia. The etiologies are listed in Figure 1 including the estimated relative contributions and the most frequent diagnosis within the subgroup underlined in red..

**Figure 2** Diagnostic algorithm of hypernatraemia

We **hypothesize** that in patients with hypernatraemia, copeptin levels overall will be higher as compared to patients without hyponatraemia, however, with a wide range (1.7pmol/L (detection limit) to 12pmol/L). Analysing the subgroup of patients with hypernatraemia, we assume that in patients with Diabetes insipidus, copeptin levels will be markedly decreased (i.e. 1.7-2pmol/L), moderately increased (8pmol/L) in hypervolemic hyponatraemia and markedly increased in hypervolemic hyponatraemia (12pmol/L).

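### The hyponatraemia contrast uses a control with no upper sodium limit, so it includes hypernatraemic patients whose copeptin the protocol expects to be raised

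*Protocol*

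**What the plan says.** Protocol section 2.2 A, Diagnostic Study, states that hyponatraemia "will be defined as serum sodium concentration below 135 mmol/L". It expects this disorder in a fifth of the cohort: "wee expect a prevalence of around 20 % (i.e. around 75 patients of the 350 patients". The hypothesis for the group as a whole is "In patients with hyponatraemia, copeptin levels will be lower as compared to patients without hyponatraemia".

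The Hypernatremia paragraph gives the other threshold: "Hypernatremia will be defined as a rise in the serum sodium concentration to a value exceeding 145 mmol/L". On frequency it says "we expect 10 % (i.e. around 45 patients) to have hypernatraemia". On direction it says "in patients with hypernatraemia, copeptin levels overall will be higher as compared to patients without hyponatraemia". Within hypernatraemia it expects low copeptin in diabetes insipidus (1.7-2 pmol/L) and raised values of 8 and 12 pmol/L in two other subgroups.

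The Statistical Analyses text that follows lists two-group tests (t-test, Mann-Whitney) and multigroup tests (analysis of variance; Kruskal-Wallis with Bonferroni post-hoc comparisons). All are two-tailed at 0.05, and the groups are not named. It also plans a Spearman correlation of copeptin with sodium. The protocol nowhere defines a normal-sodium group or takes hypernatraemic patients out of the hyponatraemia control.

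**The concern.** A statement that copeptin is low in hyponatraemia is naturally read as low relative to undisturbed sodium. The stated control mixes two kinds of patient: those with sodium 135-145 mmol/L and those above 145 mmol/L. The second kind is expected to have raised copeptin, which lifts the control in the direction that favours the hypothesis. A significant finding could therefore arise, in part or entirely, because copeptin is high in hypernatraemia, with no difference between hyponatraemia and normal sodium.

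The hypernatraemia hypothesis uses the same non-hyponatraemic reference, which as written contains the hypernatraemic patients themselves. If that is a slip for the non-hypernatraemic patients, the reference then contains the hyponatraemic patients, who are expected to be low: the mirror-image problem. Correcting that wording alone would leave the hyponatraemia contrast as it is.

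**Working it through.** **Cohort size.** Section E gives about 480 eligible patients, 80% consent and 10% loss: 480 × 0.80 × 0.90 = 345.6, which agrees with the stated figure of about 350.

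**Group sizes.** The percentages and counts in the Diagnostic Study text do not match, so both sets are carried.

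| Basis | Hypo | Normal | Hyper | Control as written | Hypernatraemic share w |
|---|---|---|---|---|---|
| Percentages (20%, 10% of 350) | 70 | 245 | 35 | 280 | 35/280 = 12.5% |
| Counts (75, 45) | 75 | 230 | 45 | 275 | 45/275 = 16.4% |

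**Artificial difference in means.** Suppose hyponatraemic and normal-sodium patients both average 5 pmol/L. This is an assumption: the protocol gives about 5 for the whole cohort. The control then exceeds the hyponatraemic group by w × (hypernatraemic mean − 5).

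- Hypernatraemic mean 8: 0.125 × 3 = 0.38, or 0.164 × 3 = 0.49 pmol/L.
- Hypernatraemic mean 12: 0.125 × 7 = 0.88, or 0.164 × 7 = 1.15 pmol/L.

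For scale, the protocol's expected difference between the cohort and healthy controls is 5 − 4 = 1 pmol/L.

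**Chance of rejection.** No SD is given, so the separation between hypernatraemic and normal-sodium copeptin is expressed as an assumed AUC. If hyponatraemia equals normal sodium, the expected AUC of the written contrast departs from 0.5 by w × (AUC − 0.5). The null standard error of the Mann-Whitney AUC is √[(n1 + n2 + 1)/(12 n1 n2)].

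Worked example, percentages, AUC 0.8:

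- Shift = 0.125 × 0.3 = 0.0375.
- SE = √[351/(12 × 70 × 280)] = 0.0386.
- Shift/SE = 0.97.
- Chance of a two-sided 5% rejection ≈ 1 − Φ(1.96 − 0.97) ≈ 16%.

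Simulation of the same null gives 15%. Simulated rejection rates in all settings:

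| Assumed AUC, hyper vs normal | 70/245/35 | 75/230/45 |
|---|---|---|
| 0.6 | 6% | 7% |
| 0.7 | 9% | 14% |
| 0.8 | 15% | 25% |
| 0.9 | 23% | 41% |

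Against the normal-sodium patients alone, the rate stays at about 5% in every setting. With lognormal medians of 8 versus 5 pmol/L and an assumed log-SD of 0.8 down to 0.4, the rates are about 8-15% (percentages) and 10-24% (counts).

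**When the direction changes.** Take diabetes insipidus at 1.85 pmol/L (the middle of 1.7-2) and the rest of hypernatraemia at h. The hypernatraemic mean falls to 5 when the diabetes insipidus share is (h − 5)/(h − 1.85). That is 3/6.15 = 49% for h = 8 and 7/10.15 = 69% for h = 12. Below that share the control is pushed up; above it, down. The expected mix of causes is in a figure that is not readable here.

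**The case against.** The strongest reply is that the sentence is a hypothesis, not an analysis instruction. The Statistical Analyses text assigns no test to it, already offers a three-group test, and could be completed in a statistical analysis plan. This stands in part: the Mann-Whitney test used above is one of the listed options, not a fixed choice. But the control is more than an omitted detail. It is the only comparator stated, and taken literally it gives a biased answer about normal sodium. The Spearman correlation does not replace it, because hypernatraemic patients can drive a correlation across the whole sodium range.

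A reader might infer that the planned test loses its 5% error rate. The protocol does not support that: for the literal contrast, hyponatraemic against everyone else, the test keeps its level. The inflation concerns only the interpretation as a difference from normal sodium.

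A reader might also infer that the diagnostic objective as a whole is compromised. It is not. The stated aim is the differential diagnosis of hyponatraemia, and those comparisons are made among hyponatraemic patients without this control.

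Finally, size and direction cannot be fixed from the protocol. The SD and the mix of causes are not given, 8 pmol/L is one subgroup's value, and 5 pmol/L is the cohort's. That is a fair limit, and it is why only ranges are given.

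**Conclusion.** The point holds for the secondary contrast between hyponatraemic and non-hyponatraemic patients. By the protocol's own definitions, 12.5-16.4% of the control has the opposite sodium disorder, and the protocol expects that group to have higher copeptin overall. With no true difference from normal sodium, the chance of a significant result would be about 9-41% across the two sets of group sizes at assumed AUCs of 0.7-0.9, and 6-7% at 0.6.

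These rates rest on three assumptions: a Mann-Whitney test, identical copeptin in hyponatraemia and normal sodium, and hypernatraemic copeptin raised as hypothesised. A wholly spurious finding is the extreme case, not a prediction. If diabetes insipidus makes up a large share of hypernatraemia, the bias shrinks or reverses, and a real deficit in hyponatraemia could then be masked. In either case the contrast cannot be interpreted cleanly while its bias depends on an unspecified case mix. The study is exploratory and sized on the prognostic question, so this is a change worth making rather than a threat to the main aims.

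**What to change.** In the Hyponatremia and Hypernatremia paragraphs of section 2.2 A, define the reference group for both hypotheses as patients with sodium 135-145 mmol/L, and compare each disorder with it. The Kruskal-Wallis test with Bonferroni post-hoc comparisons already listed under Statistical Analyses can carry this as a three-group analysis. The change of reference group alone removes the bias; the three-group route is optional.

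No new data are needed. The control loses 35 patients (280 to 245) or 45 (275 to 230). With a common SD, the standard error of the hyponatraemia comparison is proportional to √(1/n1 + 1/n2). It rises from 0.1336 to 0.1355 (1.4%) or from 0.1303 to 0.1330 (2.1%), which is negligible for power. If the three-group route is taken, the Bonferroni correction costs some further power, and that should be accepted openly.

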**Hypernatremia**

Hypernatremia will be defined as a rise in the serum sodium concentration to a value exceeding 145 mmol/L [3]. Again, we will use a standardized clinical algorithm based on clinical and laboratory parameters to evaluate the aetiology of hypernatraemia.

Of all 350 patients included (see sample size considerations) we expect 10 % (i.e. around 45 patients) to have hypernatraemia. The etiologies are listed in Figure 1 including the estimated relative contributions and the most frequent diagnosis within the subgroup underlined in red..

**Figure 2** Diagnostic algorithm of hypernatraemia

We **hypothesize** that in patients with hypernatraemia, copeptin levels overall will be higher as compared to patients without hyponatraemia, however, with a wide range (1.7pmol/L (detection limit) to 12pmol/L). Analysing the subgroup of patients with hypernatraemia, we assume that in patients with Diabetes insipidus, copeptin levels will be markedly decreased (i.e. 1.7-2pmol/L), moderately increased (8pmol/L) in hypervolemic hyponatraemia and markedly increased in hypervolemic hyponatraemia (12pmol/L).

**Statistical Analyses**

Copeptin levels will be assessed in a blinded batch analysis upon completion of the plasma asseveration.

Discrete variables will be expressed as counts (percentage) and continuous variables as means ± standard deviation (SD) or median (interquartile range), unless stated otherwise. First, the overall prevalence of hyponatraemia in neurological and neurosurgical patients will be assessed. Frequency comparison will be done by chi-square test. Two-group comparison of normally distributed data will be performed by Students t-test. For multigroup comparisons, one-way analysis of variance with least square difference for posthoc comparison will be applied. For data not normally distributed, the Mann-Whitney-U test is used if only two groups are compared. The Kruskal-Wallis one-way analysis of variance with Bonferroni’s multiple posthoc test will be used if more than two groups were being compared.

Furthermore we will do a correlation analysis of copeptin levels with sodium levels, serum osmolality and other diagnostic laboratory parameters. Correlation analyses will be performed by using Spearman rank correlation. Levels that are non-detectable will be assigned a value equal to the lower limit of detection for the assay. All testing will be two-tailed and P values less than 0.05 were considered to indicate statistical significance. Scatterplot data will be shown with GraphPad Prism®, Version 4.00 for Windows (GraphPad Software, San Diego California, USA).

We will then compare the diagnostic accuracy of Copeptin levels with other potential biomarkers for sodium imbalance, e.g. atrial natriuretic peptide (ANP) and B-type natriuretic peptide (BNP). The ability of Copeptin to foresee sodium disbalance before it becomes evident by laboratory analysis will be assessed. Therefore we will correlate Copeptin levels with sodium level changes over time.We will construct receiver operating characteristic (ROC) curves and determine the areas under the receiver operating characteristic curve (AUC). The sensitivity and specificity to predict the correct diagnosis of hyponatraemia will be determined, based on the above standardized algorithm [32]. This ascertainment will be done retrospectively on the basis of the review of the complete patient charts by two study investigators, blinded to each other’s diagnosis. Discordant cases will be mutually discussed and resolved. Patients will be managed as usual according to the state of the art treatment.

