**D. Potential risks, Adverse events and Monitoring board**

We consider the risks of this study to be minor and limited to the following

Blood Loss: 7.5ml of EDTA-plasma will be additionally drawn during each routine blood sampling. The total additional blood loss for this study will be less than 50 ml.

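### The correlation of copeptin with sodium change does not measure whether copeptin foresees sodium imbalance, and its sign depends on the aetiology mix and on whether sodium is falling ill or being corrected

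*Protocol*

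**What the plan says.** The Statistical Analyses section of the diagnostic study (Protocol 2.2, after the Hypernatremia text) sets a distinct aim: "The ability of Copeptin to foresee sodium disbalance before it becomes evident by laboratory analysis will be assessed". The next sentence fixes the method: "Therefore we will correlate Copeptin levels with sodium level changes over time". The type of coefficient comes from the general rule in the same section: "Correlation analyses will be performed by using Spearman rank correlation". Tests are two-sided at 0.05.

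ROC curves and AUCs follow directly, but their target is stated as "The sensitivity and specificity to predict the correct diagnosis of hyponatraemia will be determined, based on the above standardized algorithm". That diagnosis is made retrospectively from the complete charts by two investigators.

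The expected copeptin levels are in A. Objectives. Overall, "included patients will have moderately but significantly higher copeptin levels (around 5pmol/L"). Within hyponatraemia they are 12 pmol/L for SIADH, 8 for hypovolaemic and below 2 for hypervolaemic cases. Within hypernatraemia, for diabetes insipidus, "copeptin levels will be markedly decreased (i.e. 1.7-2pmol/L"), and 8 and 12 pmol/L for the two other groups. The same section also states overall directions: copeptin lower in hyponatraemia and higher in hypernatraemia.

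Section D says "7.5ml of EDTA-plasma will be additionally drawn during each routine blood sampling", with total extra blood loss under 50 ml.

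**The concern.** To foresee an imbalance is to predict, in a patient whose sodium is still normal, that it will leave the normal range. The named method differs from this in two ways.

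- **Population.** The inclusion criteria set no sodium limit, patients are treated as usual, and the sentence on the correlation does not restrict it to normonatraemic patients. A patient who arrives hyponatraemic and is corrected has a rising sodium. A patient who becomes hyponatraemic has a falling one. With the same copeptin, the two push the coefficient in opposite directions.
- **Shape.** The protocol expects copeptin on both sides of 5 pmol/L within each disorder. One monotone, signed coefficient over both disorders cannot represent that. Strong effects of single aetiologies can offset each other.

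At stake is a stated aim of the diagnostic study. A null coefficient could hide a real early-warning signal, and a significant one would not show that copeptin precedes onset.

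**Working it through.** **Plan's own figures.** The protocol gives no expected value for this correlation. Its sample figure reproduces: 480 × 0.80 × 0.90 = 345.6, stated as about 350. Its prevalences of 20% and 10% give 0.20 × 350 = 70 and 0.10 × 350 = 35. The text prints about 75 and 45; 70 and 35 are used here, leaving 245 normonatraemic.

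**Inputs from the protocol.** Copeptin is 12, 8 and <2 pmol/L in hyponatraemia (SIADH, hypovolaemic, hypervolaemic), and 1.7-2, 8 and 12 in hypernatraemia. The overall level of 5 is applied to normonatraemic patients.

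**Assumptions, not in the protocol.** The value 1.85 stands for both <2 and 1.7-2. Copeptin is lognormal with log-SD 0.3, 0.5 or 0.8. Sodium change is -8, 0 or +8 mmol/L with SD 3. Hypernatraemia aetiologies have equal shares. The hyponatraemia shares are varied, because the figures that hold the protocol's estimates are not shown in the text available.

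**Step 1: all changes are onsets.** 1,000 data sets of 350 per setting, Spearman, two-sided 0.05:

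| Hyponatraemia mix (SIADH / hypovolaemic / hypervolaemic) | Mean rho, log-SD 0.3 / 0.5 / 0.8 | Significant |
|---|---|---|
| equal thirds | -0.05 / -0.03 / -0.02 | 18 / 11 / 9% |
| 70 / 20 / 10 | -0.25 / -0.21 / -0.15 | 100 / 98 / 82% |
| 15 / 15 / 70 | +0.23 / +0.20 / +0.15 | 97 / 94 / 79% |

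The levels per aetiology are the same in every row. Only the mix changes, and it moves the coefficient from clearly negative through zero to clearly positive.

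**Step 2: onset against correction.** Mix 70/20/10, log-SD 0.5, with a share of the changes reversed in sign to represent correction of an imbalance already present:

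- no corrections: rho -0.21
- half corrections: rho 0.00
- all corrections: rho +0.21

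**Step 3: what separate contrasts show.** With the same levels and a coefficient of variation of 0.5 to 1.0, the AUC against normonatraemic patients is 0.77-0.91 for SIADH. For diabetes insipidus it is 0.07-0.20, or 0.80-0.93 when reversed, since copeptin is low there. Each aetiology is well separated; the pooled signed coefficient loses this.

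**Step 4: the overall directions.** With x the hypervolaemic share and the rest split evenly between 12 and 8, the hyponatraemia mean is 1.85x + 10(1 - x). It falls below 5 when x > 5/8.15 = 0.61. Equal shares give (12 + 8 + 1.85)/3 = 7.3, which does not fit the protocol's statement that copeptin is lower in hyponatraemia.

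**The case against.** A reader might infer that the protocol's own levels make the correlation close to zero. They do not. That needs equal aetiology shares, which contradict the stated overall direction (Step 4). The overall directions, lower in hyponatraemia and higher in hypernatraemia, imply a positive association that Spearman can detect, as the third row of the table shows. This stands. Yet a significant positive rho would mean that low copeptin goes with falling sodium, the reverse of what is expected in SIADH, so significance would still not answer the aim.

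A reader might also infer that repeated samples are treated as independent. The protocol does not say so. It names no unit of analysis, and an analysis plan may settle it. If samples were pooled naively, the null rejection rate depends on how change is defined: from under 1% to 3% with successive differences, and 10-29% with change from a common baseline or with both variables correlated within patient. At under 50 ml, 50/7.5 = 6.7 allows at most six samples, but six is a ceiling and not a plan. The point is conditional and secondary.

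Other objections carry weight:

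- The levels used are for established imbalance; the protocol gives none for the period before onset. The simulations show how the statistic behaves, not how much early-warning signal would be lost.
- The correlation is not the only analysis. ROC curves and comparisons across several groups are planned, and the latter do not cancel across aetiologies. But neither is directed at later onset.
- Foreseeing imbalance is in neither the numbered objectives nor the hypotheses, the sample size rests on the prognostic question, and the study is exploratory. This limits the weight of the point.
- Population and time window could be left to an analysis plan. The choice of a correlation was not left open; the protocol makes it.

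**Conclusion.** The point holds in this form: the method that the protocol names for the aim of foreseeing imbalance does not measure prediction of a later onset. As written, nothing separates onset from correction, and a coefficient pooled over both disorders can cancel or reverse with the case mix. Its mean ran from roughly -0.25 to +0.23 over the mixes tried, near zero with equal shares. These figures rest on the assumed mixes, sodium changes and spread, and on levels for established imbalance. That the method does not match the aim follows from the text and needs none of them. The change is worth making, but it concerns one secondary, exploratory analysis and not the study's main conclusions.

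**What to change.** For this aim, replace the correlation with the following, and keep the correlation as descriptive:

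- **Population:** patients with sodium 135-145 mmol/L at the first copeptin sample, one row per patient.
- **Outcomes:** new hyponatraemia (<135 mmol/L) and new hypernatraemia (>145 mmol/L) before discharge, analysed separately.
- **Model:** logistic or cause-specific regression on log copeptin, with curvature allowed, adjusted for starting sodium and for cohort (stroke or neurosurgical).
- **Report:** the gain in AUC over starting sodium alone, with its confidence interval.
- **Repeated samples, if used:** a mixed model or cluster-robust standard errors.

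The cost is wording and modest analysis work; no new patients or samples are needed. Patients already abnormal at the first sample leave this one analysis, and the number of new events may be small. Hypernatraemia is the tighter case: about 35 patients are expected in all by the 10% prevalence, including any already abnormal at the first sample. The model should be kept correspondingly small and its result presented as exploratory.
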